
**Figure 2. F2:**
[figure not shown]
Close to Home theory of change. C2H: Close to Home.

### Study Design

#### Overview

To evaluate the C2H program, we implemented a quasi-experimental, parallel group evaluation using a cluster-matched control design with 24-month follow-up (ClinicalTrials.gov ID#: NCT05206994). Given that intervention sites were preselected before the evaluation, we used propensity score matching to identify 11 control sites, for a total of 22 communities enrolled in the study. An allocation ratio of 1:1 was used. Using an SN sampling design, data collection was conducted with youth program participants and two layers of their SN to assess the diffusion of the intervention effects to socially connected peers within each community. Additionally, school-based data collection of all high school students at the primary high school in each community was conducted via the California Healthy Kids Survey. This research evaluation was conducted in partnership with CDPH, VALORUS (the TTA provider), the 22 community-based organizations, a community research advisory board (RAB) made up of staff from the C2H-implementing NGOs, and a youth research advisory board (YRAB) made up of youth from the intervention and control communities.

#### Control Condition Sites

Given preselection of C2H sites, a natural experiment using control matching, rather than randomization, was the most rigorous design possible. Matching was conducted with the goal of nearing exchangeability [36]. A youth development program called 4-H was selected to be the control because it (1) recruits teams of prosocial youth interested in helping their community who are supported by adult volunteers, much like C2H, (2) operates in nearly every county across California, allowing for enough variability to optimize matching, and (3) was active during the same time as C2H implementation. The 4-H clubs engaged youth in prosocial learning projects (eg, agriculture, computer science, and art), with adult volunteers as allies to those efforts, yet had no programming related to SV or DV. More details about the 4-H program can be found online [37]. Participants could withdraw from the program at any time. Propensity score matching used a complete list of all local 4-H programs with at least 8 registered youth ages 14‐24 years and not located in a county with an agency implementing C2H or receiving CDPH funding for SV prevention. Propensity scores were assigned based on zip code–level characteristics relating to SV or DV: percent Black population, percent Hispanic population, percent completed bachelor’s or graduate school, percent population under the federal poverty line, criminal rape rate per 100,000 people, presence of a higher education institution, and percent rural population. The 4-H club with the highest propensity score matched to each of the C2H sites was screened by a member of the research team via a short phone call with the adult club facilitator. Screening was conducted for the following inclusion criteria: (1) at least 8 registered youth ages 14‐24 years; (2) stability of club over the past 6 months; (3) in a geographic zip code with no rape crisis center implementing C2H; (4) no violence prevention programming or education offered by the 4-H club; and (5) adult club facilitator willingness to engage in this study. Ultimately, in terms of propensity scores, 5 of C2H sites were matched with the best matched 4-H program, 4 with the second, third, or fifth best match, and 3 that proved difficult to match, which ended up with the 30th, 36th, and 45th best match (out of 69 clubs; see the Data Analysis section for details on analytical approach to address baseline differences). The 4-H clubs with higher propensity scores declined to participate or were ineligible due to an unstable club membership or leadership (discovered upon discussing with the club leader), concerns about parent perceptions of the topic of this study, or being unresponsive to recruitment efforts. Ultimately, the way self-selection played a role in the final control sample likely improved exchangeability between intervention and control communities in that all of the intervention C2H groups had stable club membership and leadership, had low parental concerns about the topic of this study, and had responsive leaders to recruitment efforts.

#### RAB Engagement

A provider RAB and a YRAB were recruited and engaged to inform the development of study protocols, survey instruments, study implementation, as well as ensure the feasibility and acceptability of this study. RAB and YRAB members are compensated for their time. The RAB is made up of key staff from CDPH Injury and Prevention Branch, TTA providers, including the C2H founder and staff from California’s SV coalition (ValorUS), and staff from the 11 C2H local programs. Initially, the RAB met bimonthly to deepen the conceptualization of the theory of change and mechanisms through which C2H was reducing SV and DV in their communities, to guide development of study protocols to ensure coordination and synchrony with C2H implementation, and to provide feedback on outcome and process data collection instruments. Since data collection began, the RAB met on a quarterly basis to provide feedback on implementation and to inform the refinement of study protocols. The YRAB, made up of 7‐10 youth participants of C2H or 4-H programs, engaged in parallel activities throughout the development of study protocols and instruments. The RAB and YRAB will be engaged in the interpretation of results and development of recommendations for future implementation of C2H.

#### Ethics

Research ethical and safety protocols for this study adhered to recommendations issued by the World Health Organization for research on violence against women [38]. The current study protocol and analysis plan are registered on ClinicalTrials.gov (NCT05206994).

#### Data Sources

Three data sources were used in this evaluation: (1) process data from program staff, (2) participant SN data, and (3) data from the California Healthy Kids Survey.

#### Process Data Collection

Process data were collected via monthly surveys with program staff and quarterly consultations with program staff and TTA providers to monitor intervention fidelity. For C2H programs, a phase-specific checklist that reflected the guidelines for implementation of each phase was used to measure fidelity, quality, and frequency of interaction with the target community, C2H participant engagement, and barriers and facilitators to implementation. For control programs, qualitative process data were collected with adult volunteer leaders every 6 months during the intervention period, which included participant-level program dosage estimates, any unanticipated exposure to violence prevention programming, and exogenous changes in the community and schools around SV that may have impacted knowledge, awareness, and/or behavior.

#### SN Primary Data Collection

##### Youth Recruitment

Youth program participants ages 14‐24 years were recruited to this study from each C2H site and the matched control site within 6 months of one another (henceforth, “egos”). Ego recruitment was initiated at a C2H site as soon as the site had recruited and established a youth team to begin a new cycle of C2H implementation, between October 2021 and May 2023. Due to major disruptions caused by the COVID-19 pandemic, C2H implementation began at different time points across sites; 7 sites started in the fall of 2021 and 4 sites started in the fall or winter of 2022‐2023.

To recruit youth, the cofirst author attended a regular C2H/4-H meeting (in-person or virtual), shared this study’s purpose, the SN recruitment process, the risks and benefits of participating, compensation, and, after all questions were answered, invited youth to participate in this study. Those who were interested in participating were sent a personalized link using a provided phone number or email address. Research staff provided tablet devices, device chargers, a Wi-Fi hotspot, and snacks to participants as needed. After this initial meeting, as new youth were recruited to the C2H/4-H groups, research staff continued recruitment as needed, providing virtual or in-person survey orientations as needed to invite all C2H/4-H members to participate and maximize ego recruitment.

Youth accessed the survey via a Qualtrics link, which began with an electronic informed assent or consent form, proceeded to eligibility screening, and concluded with the full survey instrument. Eligibility criteria included being between the ages of 14 and 24 years, currently living in California, being a current participant in a C2H or 4-H group (or for nominated alters, being nominated by a current participant), and providing informed consent or assent. Youth who declined to participate or were not eligible to participate were offered an alternative online activity to do while others were taking the survey to conceal participation. The survey took approximately 40 minutes to complete. At the end of the survey, youth were asked to provide their contact information so that they could receive online incentives and be recontacted for retention check-ins and for the 24-month follow-up survey. Participants received a US $20 online gift card within 24 hours of completing the survey. All survey participants were provided with an online list of resources (eg, SV, sexual harassment and DV advocacy, LGBTQ+ support, and mental health services).

To gather data on SN members (henceforth, “alters”) of the egos, the survey included SN name generator questions to prompt participants to identify up to 10 peers from their SN (ie, “alter 1 s”). Refined via pilot testing, the name generator question prompt was “of the people in your life who live, go to school, or work in or very close to [geographic location of the community site] and are between the ages of 14 and 24…” and the specific name generator questions were “Who do you consider a close friend (including any dating/romantic partners you have)?” “Who are the people that you participate in activities with and who you also consider a friend (activities could include things like sports, jobs, online or in-person meetings, after-school clubs, or other groups involving people around your age)?” and “Besides your close friends, who do you talk to about issues that are important to you?”

Participants were then shown within the survey a list of all unique individuals they nominated, and participants were asked to rank their level of closeness to each peer. For their six highest-ranked nominated peers, participants are asked to answer questions about how each listed peer would respond to scenarios relating to SV behaviors (ego-centric SN data) and provide the peer’s contact information (first name, first two initials of last name, phone number, or email) for recruitment to the SN sample. After participants submitted their peer nominations, the Qualtrics platform was programmed to automatically send survey invitations to the nominated peers via text message or email. At the same time, participants were prompted within the survey to personally inform their nominated peers about this study, with sample text message language provided to support their outreach. This personal outreach was encouraged to help reduce participants’ concerns about nominating peers and to “warm up” peers for the incoming communication from this study’s team. After the initial invitation was sent to nominated peers, they were reminded about the opportunity to participate after 2 days, and contact information was deleted after 14 days.

Once a nominated peer accessed the survey link (on their own device, in a location or time of their choice), they completed the same assent or consent form as egos, followed by a modified eligibility screening that included confirmation of being between the ages of 14 and 24 years, being new to the survey (ie, not having taken it before), and knowing the person that nominated them. Additionally, when a nominated peer accessed the survey link, a US $10 incentive was sent to their ego nominator in acknowledgment of their time and effort to recruit their peer. Once screened, these peers became “alter 1s,” received the same survey, the same opportunity to nominate up to 10 peers (yielding potential “alter 2s”), and the same request for providing their contact information and their nominated peer’s contact information as the egos. Upon completion of a survey by an alter 1, the alter 1 received a US $20 gift card within 24 hours. Alter 2 recruitment and participation mirrored that of alter 1 s except they were not asked to nominate peers or provide peer contact information. Alter 2 s received a US $25 gift card for taking the survey, and alter 1, who nominated them, received US $10 when they accessed the survey link. Alter 1 and alter 2 surveys included an embedded video created by the YRAB explaining this study and the risks and benefits of participation, providing similar information as is provided during the ego survey orientation.

##### Informed Consent and Assent

All study participants were notified of potential risks and risk mitigation strategies via informed assent (participants younger than 18 years) or consent (participants 18 years and older). Voluntary informed assent or consent was obtained from participants electronically via a digital signature before participants began the survey. Participants had the option to print the assent or consent document or receive a copy via email for their records. The informed assent or consent document contained written details about this study, risks and benefits to participants, contact information for participant concerns with this study, and the contact information of the principal investigator (PI) and approving ethics board (see Multimedia Appendix 1: informed consent and assent templates). The research staff who conducted the survey orientations verbally explained important details from the informed assent or consent form and gave the opportunity for attendees to ask questions at any point before, during, or after survey administration.

A waiver of parental permission for participants aged younger than 18 years was requested because the research involves no more than minimal risk to the participants, and the waiver does not adversely affect the rights and welfare of the participants. This waiver was approved by the UC San Diego ethics board (protocol #201920). While parental permission was waived due to the minimal risk for participants, parents of C2H and 4-H participants aged younger than 18 years were given the opportunity to refuse to permit their child to participate in this study to comply with research requirements of the California 4-H Youth Development Program and ensure identical recruitment processes for intervention and control youth. This option was provided only to participants (“egos”) in the intervention or control programs because alters were not subject to 4-H requirements. One week before the survey orientation and recruitment meeting, C2H and 4-H youth facilitators emailed parents of all those participants aged younger than 18 years a link to an online opt-out form allowing them to decline their child’s participation in the survey. Parental opt-out remained available until the day of the survey orientation.

##### Risk Mitigation

Given the topic of this study and this study’s population, risk mitigation was a top priority throughout implementation, including in this study’s design, data collection, data management, and data analysis phases. The greatest risk for study participants aged younger than 18 years included loss of confidentiality. To maintain confidentiality, all personally identifying information was immediately collected in a survey form separate from the survey responses and stored in a separate, password-protected file that was saved on a secure server through the UC. In this file, participant names were removed and replaced with a participant ID, and only two people from the research team had access to the contact information file. Participant contact information was maintained in this secure file for the purpose of recontact for follow-up data collection and was deleted as soon as study participation ended. This procedure was described to participants in the consent or assent form, in addition to an assurance that names and other identifying information would never appear in reports of this study’s results.

This study’s risk section of the consent or assent form also outlined risks related to the SN study design, making it clear to participants that if they elected to nominate peers, those peers would know that they had nominated them, but would not know that they had participated in this study.

All participant responses were protected by a certificate of confidentiality issued by the CDC. This information was shared with participants in this study’s risk section of the consent or assent form. Circumstances under which researchers would have to disclose participant information provided as part of this study were outlined in the same consent or assent form section so that participants could make an informed choice about what they chose to disclose. Circumstances in which the certificate would not apply included reporting child abuse, a danger to themselves or others, sexual contact between a minor and an adult, and if a participant requested that their information be shared. PI and HRPP contact information was provided to all participants, should any participant have concerns. No such disclosures occurred during data collection.

Concerning emotional risks related to the survey content on SV and DV, the following content warning was provided in this study’s risk section of the consent or assent forms:

*The survey includes questions on experiences of and exposure to sexual violence and dating violence. You may feel nervousness or discomfort while answering these questions. In case you feel any discomfort, you can decline to answer questions about your experiences with sexual violence and dating violence, or you can withdraw at any time by simply exiting the survey. Choosing not to answer any question or withdrawing from the survey will not result in any penalty.*

Additionally, similar content warnings were provided within the survey before participants viewed sensitive questions. Survey content warnings also reminded participants that they were free to skip questions or terminate their participation at any time without penalty.

All study participants were provided with resources related to the survey topic following study participation. Resources were provided to participants within the survey module, and included the RAINN (Rape, Abuse & Incest National Network) National Sexual Assault Hotline, a RAINN information page for LGBTQ+ survivors of SV, the Trevor Project helpline, and Forge Forward’s information page for transgender survivors of violence.

Study protocol breaches, breakdowns of the consent or assent process, violations of participant confidentiality, participant complaints, and any serious issues or adverse events were to be reported immediately to the PI, who was responsible for filing an incident report with the HRPP within 24 hours. Incident reports would have included a detailed account of the problem, the date of occurrence, the date the event came to the attention of the PI, the impact on the participant, and the corrective action taken. No such events occurred during the course of data collection. All risk mitigation protocols were approved by HRPP.

##### Recontacting and Retention for SN Data Collection

All baseline participants were contacted 6, 12, and 18 months after completion of their baseline survey by research staff, using the contact information they provided. Retention check-ins took 1‐3 minutes to complete and served to verify contact information and to remind participants of the 24-month follow-up survey. To build rapport and connection with participants in this study, retention check-ins were responded to individually by a research staff member in real-time; participants were invited to follow this study’s social media (@YouthConnectStudy) to receive posts related to this study and feel a sense of membership in this study; updates on milestones were shared; and participants were invited to join the study’s YRAB. The YRAB has helped guide these retention strategies and manages the social media account, creating and posting content about implementation of this study, about SV-related topics, and updates about the research, a strategy that has been successful in previous longitudinal studies of California youth [39].

##### Follow-Up SN Data Collection

Implementation of the four C2H phases required a minimum of 12 months. Follow-up data were collected 24-months postbaseline. Follow-up surveys were self-administered via an online link by the youth. We reached out to participants when 24 months had passed since their baseline participation via the provided contact information, updated via retention efforts, and reminded them weekly of the opportunity to participate in follow-up data collection to minimize loss to follow-up. Participants received a US $50 incentive for completing the follow-up survey. See Multimedia Appendix 2: Close to Home evaluation participant timeline.

##### SN Data Statistical Power

We powered the matched cluster evaluation trial to have .80 power to detect a reduction in 12-month incident SV (the primary outcome) at α<.05. We estimated we would have a follow-up sample of 791 youth study participants (baseline sample: n=953, 791/953, estimated 85% retention at follow-up) from the SN data collection across 22 study sites (11 C2H and 11 control; estimated 36 youth per cluster). We assumed that the average baseline 12-month incidence of the primary outcome would remain constant for the control group at follow-up (107/395, 27% past 12 months SV). The minimal detectable effect would therefore be a 32% (.27 × .32) reduction in SV (71/396, 18% for 12 months incidence at follow-up). Reducing SV by 32% is feasible, given that a previous rigorous evaluation of the shifting boundaries SV prevention model detected a 43% and 50% reduction in SV [40,41]. Furthermore, 37.5% (297/791) of the sample identified as a sexual and/or gender minority (ie, LGBTQ+), among whom 42.4% (126/297) report SV. Estimating the minimal detectable effect for this subsample (297/791 of follow-up participants, 37.5%, 14 LGBTQ+ youth per site), and a 42.5% baseline incidence for LGBTQ+ controls, this study was also powered to detect a 33.5% (0.335 × 0.425=0.14; 0.425-0.14=28% for 12 months incidence at follow-up, 83/297) reduction in LGBTQ+ SV experiences.

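### The LGBTQ+ subgroup's 33.5% detectable reduction does not have .80 power at a two-sided 5% level: about 149 youth per arm give about 73% before clustering

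*Protocol article*

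**What the plan says.** SN Data Statistical Power says the trial was powered "to have .80 power to detect a reduction in 12-month incident SV (the primary outcome) at α<.05". Sidedness is not given, and neither is an intracluster correlation for the social network sample. The design is "22 study sites (11 C2H and 11 control; estimated 36 youth per cluster"), and Study Design, Overview adds that "An allocation ratio of 1:1 was used".

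For LGBTQ+ youth the section takes a subsample of "297/791 of follow-up participants, 37.5%, 14 LGBTQ+ youth per site", assumes "a 42.5% baseline incidence for LGBTQ+ controls", and concludes that "this study was also powered to detect a 33.5" percent reduction. The resulting rate is written as "0.425-0.14=28% for 12 months incidence at follow-up, 83/297".

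The main comparison in the same section uses one-arm denominators: 107/395 for control and 71/396 for intervention.

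**The concern.** The subgroup size is 37.5% of everyone followed up in both arms, and the treated arm's expected rate is printed over that same two-arm total. Once the 297 are split between arms, a drop from 42.5% to about 28% looks too small for .80 power at a conventional two-sided level, and the trial is clustered as well.

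The Discussion predicts that effects will be among the strongest in LGBTQ+ youth. A reader told that this subgroup was also powered may give its result, positive or null, more weight than the sample supports.

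**Working it through.** **Inputs (SN Data Statistical Power unless noted).** Control rate p1 = 0.425. Relative reduction 33.5%, so p2 = 0.425 × 0.665 = 0.2826. The article rounds 0.142 to 0.14 and prints 28%. Subgroup 297 = 13.5 × 22 sites. With 1:1 allocation, n = 297/2 = 148.5 per arm, or 11 × 14 = 154 at the rounded cluster size. Achieved follow-up is 746 (Results).

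**Method.** Normal approximation for two proportions, p̄ = (p1 + p2)/2 = 0.3538:

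power = Φ{ [ (p1 − p2)√n − z·√(2p̄(1−p̄)) ] / √(p1(1−p1) + p2(1−p2)) }

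Here p1 − p2 = 0.1424, √(2p̄(1−p̄)) = 0.6762 and the denominator is 0.6687. Clustering divides n by 1 + (m − 1)·ICC, where m is the number of LGBTQ+ youth per site. Every ICC below is an assumption.

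**Can the article's figure be reproduced?** Yes, with settings it does not state. At one-sided 5%, 154 per arm and ICC 0.01, the design effect is 1 + 13 × 0.01 = 1.13. The detectable reduction is then 33.75%, and power for 33.5% is 79.5%. With half of 297 per arm and a two-sided test, 33.5% is not reproduced at any ICC of zero or more.

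**Two-sided 5%, 148.5 per arm, no clustering.** (1.7350 − 1.960 × 0.6762)/0.6687 = 0.613, so power is 73.0%. With p2 rounded to 28% it is 74.6%.

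**One-sided 5%, same n.** (1.7350 − 1.645 × 0.6762)/0.6687 = 0.931, so power is 82.4%.

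**Size needed for 80%, two-sided.** (1.960 × 0.6762 + 0.8416 × 0.6687)²/0.1424² ≈ 176 per arm, or 352 in total.

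| n per arm | Assumed ICC | Power for 33.5%, two-sided | Detectable reduction, two-sided | Power for 33.5%, one-sided |
|---|---|---|---|---|
| 148.5 | 0 | 73.0% | 36.3% | 82.4% |
| 148.5 | 0.01 | 67.9% | 38.4% | 78.3% |
| 148.5 | 0.02 | 63.3% | 40.3% | 74.5% |
| 154 | 0 | 74.5% | 35.7% | 83.6% |
| 154 | 0.01 | 69.3% | 37.8% | 79.5% |
| 140 | 0 | 70.4% | 37.3% | 80.4% |
| 140 | 0.01 | 65.6% | 39.3% | 76.4% |
| 140 | 0.02 | 61.2% | 41.2% | 72.7% |

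The 140 rows use the achieved follow-up: 0.375 × 746 = 280, or 140 per arm and 12.7 per site. They assume that the 37.5% share is unchanged.

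**Was 297 used per arm?** That would give 95% power and a detectable reduction of 26.1% unclustered. An ICC of about 0.055 would be needed to return to 33.5%.

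**Denominator.** 83/297 = 27.9% is the intended treated-arm rate, so only the denominator is wrong. On one arm it is 0.2826 × 149 ≈ 42, that is 42/149 = 28.2%.

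**The case against.** The strongest reply is that the article never says two-sided. One setting, one-sided 5% with an ICC near 0.01, reproduces both social network figures: 33.75% against the stated 33.5% for the subgroup, and 31.8% against the stated 32% for the main comparison (design effect 1 + 35 × 0.01 = 1.35). Sidedness and ICC may be given in an analysis plan that is not shown.

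This stands as a possible explanation, and it is why the 73% must carry its condition. It does not settle the matter. No one-sided test is stated, and the CHKS calculation (13.8% to 11.4%, 3000 per arm) gives 80.0% power two-sided and unclustered, against 88% one-sided. Even one-sided, power at 148.5 per arm falls to 78% at an ICC of 0.01.

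A second reply is that the planned adjusted analysis could recover power. A baseline-outcome correlation of about 0.4 would bring the two-sided unclustered figure to 80%, since 148.5/(1 − 0.16) = 176.8. The article gives no such correlation and does not rest the claim on one.

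A third reply is that LGBTQ+ identity is a subanalysis and follow-up has ended, so no design decision turns on this. That is fair, and it limits the consequence to how the subgroup result is described and read.

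Three stronger readings are tempting but unsupported:
- A reader might infer from 83/297 that the calculation used 297 per arm. The 26% result above rules this out without a sizeable ICC, and the 14 per site points to about 154 per arm.
- A reader might infer that the difference-in-differences analysis must enlarge the detectable effect. For a change score the variance factor is 2(1 − ρ), so the direction turns at ρ = 0.5, and no ρ is given.
- A reader might tie the claim to the LGBTQ+-specific SV outcome. That is a separate measure, and this calculation concerns SV in general among LGBTQ+ youth.

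**Conclusion.** The concern holds in a conditional form. At a two-sided 5% level the LGBTQ+ subgroup does not have .80 power for a 33.5% reduction. Power is about 73% at 149 per arm (75% at 154) before clustering, and about 68% at an assumed ICC of 0.01. At the achieved follow-up it is about 70%, 66% and 61% at ICC 0, 0.01 and 0.02, if the 37.5% share holds. The unclustered shortfall is moderate: a detectable reduction of about 36% rather than 33.5%.

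The documents do not show that the claim is false under every reading, because an unstated one-sided test would bring it near 80%. The 83/297 is a wrong denominator whatever the sidedness, but it is a presentation error and not the source of the 33.5%.

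**What to change.** In SN Data Statistical Power:

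1. State the sidedness of the test and the ICC assumed for the social network sample.
2. Restate the subgroup's detectable reduction on its per-arm size. Two-sided, this is about 36 to 40% at 149 per arm, or 37 to 41% at 140 per arm, for an assumed ICC of 0 to 0.02. Power for 33.5% is about 61 to 73% across those ranges. Label the ICCs and the unchanged 37.5% share as assumptions. Alternatively, say plainly that the 33.5% rests on a one-sided 5% test and give its ICC.
3. Correct 83/297 to about 42/149, in line with the one-arm denominators of the main comparison.

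The cost is text and a short recalculation. No data collection or planned analysis changes, and the main analysis is not due until summer to fall 2026.
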